### Inclusion criteria

Inclusion criteria are

- elective cholecystectomy

- 18 years of age

- ability to understand the study purpose (German language)

- written informed consent

### Exclusion criteria

Exclusion criteria are

- pregnant women

- proven or suspected liver cirrhosis

- coagulopathy (platelet count below 50'000/μl)

- double medication on platelet antagonists (acetylsalicylic acid and clopidogrel)

- international normalized ratio (INR) below 1.4

- Non-German speakers

- patients who are unable to understand the study purpose.

- family members of study investigators or employees of the participating centres

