## Methods/Design

### Study objectives

The SPOCC trial is a prospective, multi-center, double blinded, randomized controlled study comparing Single-Port laparoscopic cholecystectomy with 4-port conventional laparoscopic cholecystectomy in elective surgery for symptomatic cholecystolithiasis. Patients with an indication for an elective cholecystectomy are randomized for either (A) single-port laparoscopic cholecystectomy (SPLC) or (B) conventional 4-port laparoscopic cholecystectomy (4PLC). The hypothesis of this trial is that patients undergoing SPLC will have a better outcome in cosmesis and body image 12 weeks after surgery.

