### Participating surgeons and clinics

To prevent surgeon bias, the requirements to qualify as a surgeon are equal in both arms. Since the present study represents a so-called pragmatic randomised control trial [21], the study should reflect daily practice for cholecystectomy. Operating surgeons are senior residents, chief residents, attending surgeons as well as consultant surgeons. The operating surgeon will need a minimal experience of 35 4PLC cholecystectomies,10 SPLC and must participate in a one-day workshop for SPLC.

Participating centres are the Division of Visceral and Transplantation Surgery of the University Hospital Zurich and the Department of Surgery of the Cantonal Hospital in Winterthur, Switzerland.

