### Ethics

This study is conducted in accordance with the principles of the Declaration of Helsinki and 'good clinical practice' guidelines. The principal investigator has completed a course in 'good clinical practice' certified by the Swiss Agency for Therapeutic Products (Swissmedic). The independent medical ethics committee of canton Zurich (Kantonale Ethikkommission Zürich, Switzerland) has approved the study protocol. This trial was registered at clinicaltrial.gov on January 14, 2011 (trial number: NCT01278472).

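### The INR exclusion is printed in the wrong direction: it excludes patients with normal clotting and does not stop those with a raised INR

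*Protocol article*

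**What the plan says.** The list in the Exclusion criteria section opens with "Exclusion criteria are", so a patient who meets any item on it is kept out. One of the eight items is "international normalized ratio (INR) below 1.4". Two other items concern bleeding: "coagulopathy (platelet count below 50'000/μl" and "double medication on platelet antagonists", the latter naming acetylsalicylic acid with clopidogrel. Proven or suspected liver cirrhosis, a condition that can itself raise the INR, is also excluded. The INR is mentioned nowhere else in the article, so nothing restates, explains or corrects the line.

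Three other sections give context:

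- **Study objectives:** "Patients with an indication for an elective cholecystectomy are randomized".
- **Participating surgeons and clinics:** the trial is described as pragmatic, and "the study should reflect daily practice for cholecystectomy".
- **Ethics:** the cantonal ethics committee "has approved the study protocol". That protocol is not available here.

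**The concern.** For a platelet count, a low value signals bleeding risk, so excluding values below a limit is right. For the INR, a high value signals bleeding risk, so the same word reverses the rule. Taken literally, the line turns away ordinary elective patients and leaves in those it was presumably meant to keep out.

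Two things are at stake:

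- An eligibility threshold in a surgical trial is an operative safety rule. If the approved protocol carries the same text, sites either enrolled against the written criterion or had no INR limit protecting patients with slow clotting.
- The article is the public description of who was eligible. Anyone judging which patients the results apply to, or reusing these criteria, is given the wrong rule.

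**Working it through.** No sample size, power or alpha figure is involved, so this is a check of logic and not a calculation.

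**Inputs**

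- Rule as printed (Exclusion criteria): exclude if INR < 1.4.
- Rule with the direction reversed: exclude if INR > 1.4.
- What the INR is: a clotting-time ratio normalised to normal plasma, so normal is about 1 and larger means slower. This is general knowledge about the measure and is not stated in the article.
- Illustrative INR values: 0.8 to 1.2 for normal clotting and 2 to 3 for a patient on a vitamin K antagonist. Both ranges are assumptions, since the article gives none.

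**Step 1: apply both rules to the INR line alone**

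| INR (assumed, except the limit 1.4) | As printed (< 1.4) | Direction reversed (> 1.4) |
|---|---|---|
| 0.8 | excluded | eligible |
| 1.0 | excluded | eligible |
| 1.2 | excluded | eligible |
| 1.4 | not excluded | not excluded (would be, if the limit were 1.4 or above) |
| 2.0 | not excluded | excluded |
| 2.5 | not excluded | excluded |
| 3.0 | not excluded | excluded |

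The printed rule excludes every value in the assumed normal range and none in the assumed anticoagulated range. Reversing the direction puts both right.

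**Step 2: see whether another line closes the gap**

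Take a patient with INR 2.5, normal platelets, no dual antiplatelet therapy and no cirrhosis, who meets none of the non-clinical exclusions.

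| Exclusion line | Stops this patient? |
|---|---|
| Pregnancy | no |
| Liver cirrhosis | no |
| Coagulopathy, defined by platelet count | no, platelets are normal |
| Dual antiplatelet medication | no |
| INR | no as printed; yes if reversed |
| Does not speak German | no |
| Cannot understand the study purpose | no |
| Investigator's relative or centre employee | no |

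The count is 0 of 8 lines as printed and 1 of 8 after correction. The coagulopathy line does not help, because its only stated criterion is the platelet count.

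**Step 3: compare direction with the surrounding text**

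The platelet and dual antiplatelet lines both remove patients who bleed more easily. The printed INR line is the only clotting-related item that points the other way. A literal reading would also remove nearly everyone with normal clotting from a trial that randomises elective cholecystectomy patients and describes itself as pragmatic. Both comparisons point to *above* as the intended word.

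**Step 4: rule out an artefact**

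The direction is given as a word and not as an inequality sign, so conversion from PDF could not have flipped it. Nothing in the list is blacked out, and the text does not come from an amendment log.

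**Step 5: check for effects elsewhere**

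The criterion applies before randomisation and identically to both arms, so it cannot bias the comparison. The inputs in Power of the study are an 8-point difference, an SD of 4 to 6, alpha 0.05, power 0.90 and 10% dropout. INR is not among them, so the 49 evaluable and 55 randomised patients per arm stand.

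**The case against.** The strongest case on the other side accepts the error and disputes its weight.

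- **The slip exposes itself.** Followed literally, it would make recruitment almost impossible, and a surgeon reading it beside the platelet and antiplatelet lines would see what was meant. This limits the practical risk. It does not make the text right, because a safety threshold should not depend on readers inverting it.
- **The approved protocol may be correct.** This stands. The article alone shows a misprinted criterion. Any safety or deviation consequence depends on a document that is not shown.
- **The Study objectives and pragmatic-trial statements are not strict contradictions.** This also stands. Every exclusion narrows the elective population, and the daily-practice sentence sits in a section about surgeons. Both serve only as context. The argument rests on what an INR measures and on the neighbouring bleeding-risk lines.
- **Not excluded from the trial is not the same as operated on unsafely.** Fair. The article does not say how anticoagulation is managed before elective surgery, and some patients with a raised INR would be caught by another line, such as cirrhosis. What can be claimed is that the INR line does not stop a patient with an INR of 1.4 or more, and that a patient with no other exclusion is stopped by nothing.
- **The boundary is inferred.** True. The direction is clear from context, but whether 1.4 itself is excluded is not stated.

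**Conclusion.** The concern holds. The INR exclusion is stated backwards in the article and needs correcting.

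- **Size:** one of eight exclusion lines is reversed. For a patient with a raised INR and no other exclusion, the number of lines that apply goes from 0 as printed to 1 when corrected.
- **Effect on the treatment comparison and sample size:** none.
- **Assumptions:** normal INR is about 1, with the result the same anywhere from 0.8 to 1.2, and higher values mean slower clotting. The illustrative patient is assumed to meet no other exclusion.
- **Not known:** whether the ethics-approved protocol has the same wording, and therefore whether any site acted on it.

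It is a must-fix because the criterion is an operative safety rule that cannot stand as written, not because it threatens the trial's result.

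**What to change.** Change *below* to *above* in the INR exclusion, so that patients with an INR above 1.4 are excluded. The sponsor should confirm the 1.4 threshold and state whether a value of exactly 1.4 is excluded.

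Publish the change as an erratum to the article. Check the ethics-approved protocol and, only if it carries the same wording, make a one-line amendment there as well. The cost is one word in the erratum plus, at most, that amendment. No design, sample size or analysis element changes.

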### Participating surgeons and clinics

To prevent surgeon bias, the requirements to qualify as a surgeon are equal in both arms. Since the present study represents a so-called pragmatic randomised control trial [21], the study should reflect daily practice for cholecystectomy. Operating surgeons are senior residents, chief residents, attending surgeons as well as consultant surgeons. The operating surgeon will need a minimal experience of 35 4PLC cholecystectomies,10 SPLC and must participate in a one-day workshop for SPLC.

Participating centres are the Division of Visceral and Transplantation Surgery of the University Hospital Zurich and the Department of Surgery of the Cantonal Hospital in Winterthur, Switzerland.

### Randomization

Patients have to sign an informed consent in the outpatient clinic. Randomization is performed online (internet randomization module http://www.randomizer.at[22] at the time of transfer to the operating room.

### Double blinding

Patients as well as surgeons, treating physicians and nurses are blinded until the 7^th ^postoperative day. At the end of the operation an opaque wound dressing will be applied at the four port-sites for 4PLC in both treatment arms. The dressings are occlusive and water-resistant. The skin will be closed with subcutaneous absorbable stitches. Additionally the wound will be sealed using fibrin glue to avoid any blood spots on the dressing. Each dressing will be marked with a sterile marker so that any violation of the blinding will be noticed and documented. Data collection as well as clinical controls of patients is performed by investigative independent physicians.

Any change of dressings before 7 days postoperatively are documented.

### Data collection and statistics

Informed consent of patients is performed in the outpatient clinic. Single port cholecystectomy is not offered to patients outside of the study. Data including results of questionnaires is collected on an internet-based secured study information platform [23]. The CBIS questionnaire is filled out at the outpatient clinic preoperatively as well as on the day of admission, 1 and 12 weeks postoperatively. The SF-36 quality of life questionnaire is filled out preoperatively in the outpatient clinic and 12 weeks postoperatively. Pain variables are assessed on a daily basis during hospital stay (Figure 1). Data analysis is performed in accordance with the intention-to-treat principle. Groups are compared using an Independent Samples T-test, Wilcoxon test, or Chi-square test.

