### Endpoints

The primary endpoint of the study concerns patient's satisfaction with cosmesis and body image 12 weeks after surgery. This endpoint is assessed using a validated cosmesis and body image score (CBIS) that was previously used in surgery for Crohn's disease [15] and in donor nephrectomy [16]. This score is calculated on an 8-item multiple-choice type questionnaire (Table 1) ranging between 8 and 48 points.

**Table 1 T1:** Cosmesis and Body image questionnaire consisting of a body image score (items 1 to 5) and a cosmetic score (items 6 to 8)

1	Are you less satisfied with your body since the operation? □ 1 = no, not at all □ 2 = a little bit □ 3 = quite a bit □ 4 = yes, extremely
2	Do you think the operation has damaged your body? □ 1 = no, not at all □ 2 = a little bit □ 3 = quite a bit □ 4 = yes, extremely
3	Do you fell less attractive as a result of your operation? □ 1 = no, not at all □ 2 = a little bit □ 3 = quite a bit □ 4 = yes, extremely
4	Do you feel less feminine/masculine as a result of your operation? □ 1 = no, not at all □ 2 = a little bit □ 3 = quite a bit □ 4 = yes, extremely
5	Is it difficult to look at yourself naked? □ 1 = no, not at all □ 2 = a little bit □ 3 = quite a bit □ 4 = yes, extremely
6	On a scale from 1 to 7, how satisfied are you with your scar(s)? □ 1 = very unsatisfied □ 2 = quite unsatisfied □ 3 = a bit unsatisfied □ 4 = not unsatisfied/not satisfied □ 5 = a bit satisfied □ 6 = quite satisfied □ 7 = very satisfied
7	On a scale from 1 to 7, how would you describe your scar(s)? □ 1 = revolting □ 2 = quite revolting □ 3 = a bit revolting □ 4 = not revolting/not beautiful □ 5 = a bit beautiful □ 6 = quite beautiful □ 7 = very beautiful
8	Could you score your own scar(s) on a scale from 1 to 10? (1 = ugliest scar imaginable, 10 = almost scarless)

Scores from 8 to 48.

The secondary endpoint is a combination of several variables: the quality of life 12 weeks after surgery assessed by the validated Short-Form-36 Health Survey questionnaire [17], postoperative pain assessed by a visual analogue scale daily assessment and the use of analgesics. Operative time, use of additional ports, conversion to open cholecystectomy, length of stay, costs, elapsed time before going back to work as well as intra- and postoperative complications represent aspects of the secondary endpoint. The postoperative complications are classified according to the Clavien-Dindo system [18].

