### Power of the study

A clinically relevant improvement of the cosmesis and body image score (CBIS) [15] is defined as an improvement of 20% of the cosmesis score (8 points). Given the reported standard deviation of the CBIS between 4-6 [19] and using (alpha = 0.05 and beta = 0.90), two groups of 49 patients are needed. This is based on a two-sided significance level (alpha) of 0.05 and a power of 0.90. Estimating a 10% dropout rate, which is common in randomized controlled trials [20], 55 patients will be randomized per arm.

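### The named tests for the 12-week SF-36 comparison make no use of the preoperative SF-36, so a valid secondary analysis is less precise than it could be at no extra data cost

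*Protocol article*

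**What the plan says.** Under Data collection and statistics, the protocol article schedules the questionnaire twice: "The SF-36 quality of life questionnaire is filled out preoperatively in the outpatient clinic and 12 weeks postoperatively". Under Endpoints, the outcome is the later of the two values: "the quality of life 12 weeks after surgery assessed by the validated Short-Form-36 Health Survey questionnaire". Change from the preoperative score is not mentioned.

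The analysis is given in one sentence that serves all endpoints: "Groups are compared using an Independent Samples T-test, Wilcoxon test, or Chi-square test". Apart from the intention-to-treat principle, no other feature of the between-group analysis is stated. The sentence assigns no particular test to the SF-36.

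The SF-36 has no special rank. The Endpoints section says that "The secondary endpoint is a combination of several variables", and quality of life is one of them. The sample size under Power of the study concerns the cosmesis and body image score (CBIS) only; no power is stated for the SF-36.

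**The concern.** A preoperative quality-of-life score usually predicts the same patient's later score. A two-group test on the 12-week values leaves that predictable variation in the error term, and the confidence interval is wider than the collected data require.

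The trial was sized on another outcome, with 49 evaluable patients per arm. Precision for quality of life is therefore whatever that number happens to give, and the preoperative SF-36 is the one means of improving it that is already in the schedule. Naming the adjusted model in advance also avoids a later choice among unadjusted, change-score and adjusted results.

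**Working it through.** **Inputs from the article.** Evaluable patients per arm: 49 (Power of the study). Two-sided alpha 0.05 and power 0.90 (same section). SF-36 at two time points; endpoint is the 12-week value.

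**Inputs not in the article.** The correlation r between preoperative and 12-week SF-36, and the SF-36 standard deviation. I assume r = 0.1 to 0.7 and work in SD units.

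**The plan's own figure.** There is none for the SF-36. The 49 per arm is a CBIS figure and is used here only as the number of patients expected to be analysed. The dropout step reproduces: 49/(1 − 0.10) = 54.4, rounded up to 55. The 49 itself does not follow from the stated 8 points and SD of 4 to 6, which give 6 to 12 per arm. That is a separate matter and does not affect what follows.

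**Unadjusted comparison.** Detectable difference at 90% power = √(2/n) × (z0.975 + z0.90) = √(2/49) × (1.960 + 1.282) = 0.655 SD.

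**Baseline-adjusted comparison.** Analysis of covariance multiplies the residual variance by 1 − r². Hence:

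- standard error factor = √(1 − r²)
- equivalent unadjusted n per arm = 49/(1 − r²)
- detectable difference = 0.655 × √(1 − r²) SD

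| Assumed r | 1 − r² | Variance reduction | SE reduction | Equivalent n per arm | Detectable difference (SD) | Power for 0.5 SD |
|---|---|---|---|---|---|---|
| none (unadjusted) | 1 | – | – | 49 | 0.655 | 70% |
| 0.1 | 0.99 | 1% | 0.5% | 49.5 | 0.652 | 70% |
| 0.3 | 0.91 | 9% | 5% | 53.8 | 0.625 | 74% |
| 0.5 | 0.75 | 25% | 13% | 65.3 | 0.567 | 82% |
| 0.7 | 0.51 | 49% | 29% | 96.1 | 0.468 | 93% |

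The 0.5 SD difference is illustrative only; the article gives no target for the SF-36. The powers use the normal approximation. With the t distribution and two degrees of freedom charged to the adjusted model, they are 69% unadjusted and 73%, 81% and 93% for r = 0.3, 0.5 and 0.7, so the picture does not change.

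**Would change scores do as well?** The named tests could be run on change from baseline. With equal variances at the two times, the variance relative to the 12-week score is 2(1 − r): 1.8, 1.4, 1.0 and 0.6 for r = 0.1, 0.3, 0.5 and 0.7. The corresponding values for analysis of covariance are 0.99, 0.91, 0.75 and 0.51. Change scores improve on the 12-week score only when r exceeds 0.5, and at every r in this range they are less precise than the adjusted analysis.

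**The case against.** The strongest reply is that this is a condensed article. One sentence lists tests for all endpoints, most naturally sorted by type of data, and a fuller plan that is not shown may add covariates. That stands in part: the article does not say that the preoperative SF-36 will go unused, and a t-test or Wilcoxon test on change scores would fit its words. But the article does name its methods, none of them takes a covariate, and its endpoint is the 12-week value. The point therefore concerns a stated method, not a silence.

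The second reply is that the gain is assumed. This also stands. At r = 0.1 it is 1%, which is no practical gain once a slope has to be estimated.

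Several stronger readings are tempting and are not supported:

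- **That the comparison is biased by chance baseline imbalance.** Under randomisation the unadjusted test is valid, and its standard error already allows for such imbalance.
- **That the loss falls on the main secondary endpoint.** The article ranks none of the secondary variables, and its Table 2 entry for this trial lists pain before quality of life.
- **That leaving out centre costs precision.** There are two centres, and the Randomization section states no stratification by centre that would call for a centre term. No figure allows the gain to be computed. If centre explained an assumed 1% to 5% of the variance, the standard error would fall by only about 0.5% to 2.5%.
- **That the choice between t-test and Wilcoxon test for the CBIS is a defect, or departs from the test behind the sample size.** Power of the study names no test, and allocation of tests to endpoints is something an article may leave to the full plan.

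**Conclusion.** The point holds as a minor matter of efficiency. As written, the SF-36 comparison is valid but makes no use of a preoperative score that the trial already collects. Over the assumed range of r from 0.1 to 0.7, the forgone reduction in residual variance runs from 1% to 49%. The article cannot say where in that range the trial lies. The calculation also assumes a roughly linear relation between the two scores and 49 patients per arm with both. Neither the primary endpoint nor any stated power claim is affected.

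**What to change.** State that each SF-36 score to be analysed at 12 weeks will be compared between arms by analysis of covariance, with treatment and the corresponding preoperative score as terms, and that the adjusted mean difference with its 95% confidence interval will be reported. The unadjusted test can remain as a supporting analysis. A centre term is optional.

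The change should be confined to the SF-36. It should not be carried over to the preoperative CBIS, because most items in Table 1 ask about the effects of the operation or about its scars.

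The cost is one degree of freedom per model and a sentence of analysis wording, fixed before the data are examined by arm. No additional visit, questionnaire or patient is needed.

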**Figure 1 F1:**
[figure not shown]
**Study flowchart**.

### Ethics

This study is conducted in accordance with the principles of the Declaration of Helsinki and 'good clinical practice' guidelines. The principal investigator has completed a course in 'good clinical practice' certified by the Swiss Agency for Therapeutic Products (Swissmedic). The independent medical ethics committee of canton Zurich (Kantonale Ethikkommission Zürich, Switzerland) has approved the study protocol. This trial was registered at clinicaltrial.gov on January 14, 2011 (trial number: NCT01278472).

### Surgical technique

Patients are placed in the French position with the surgeon between the legs, the cameraman (first assistant) on the left of the patient, the second assistant (facultative) on the right, the nurse near the right hand of the surgeon, and the monitor shoulder level to the patient. The endoscopic equipment in terms of optic, monitor, gas supply, suction device, graspers, monopolar hook and endobag are equal in both groups. For surgical disinfection of the skin iodopovidone is used.

